#### The feasibility of and compliance with intervention components

Attendance rates at the intervention launch, engagement with the online forum, frequency of wearing the PA monitor, frequency of group walking sessions, compliance with diary completion and attendance rates at health coaching sessions will all be summarised. The threshold of feasibility for these rates will be 70% of participants complying, respectively.

#### The feasibility of the evaluation measures

Compliance with evaluation measures will be deemed successful if no more than 20% of participants fail to provide questionnaire and accelerometer data at both baseline and week-24 follow-up.

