#### Objectives

To determine participant recruitment, retention and attrition rates.To review descriptive data to determine the feasibility of the inclusion criteria.To determine compliance and completeness of evaluation measures at all time points.To report the feasibility of delivering the intervention and evaluation measures.To explore participant compliance with the intervention.To obtain views on the acceptability of the intervention and evaluation measures.To describe device-assessed PA levels and questionnaire data outcomes of interest.

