### Measures

All PA and health measures will be assessed at baseline, week 12 and 3 months after completion (week 24). Previous literature suggests that psychological measures may take longer to change than physical measures (e.g., menopausal symptoms or PA) and therefore to reduce participant burden, only these will be taken at week 6 (table 3).

**Table 3 T3:** PA and health outcomes, outcome measures and measurement time points

Measures	Assessment tool	Baseline	Week 6	Week 12	Week 24
Device-assessed PA	Accelerometer	x	x	x	x
Menopausal symptoms	MRS	x	x	x	x
Quality of life	EORTC-QLQ-30	x		x	x
Depression and anxiety	HADS	x		x	x
Fatigue	MSFI-SF	x		x	x
Walking self-efficacy	Self-efficacy for Walking scale	x		x	x
Motivation for exercise	BREQ-3	x		x	x
Enjoyment of PA	PACES	x		x	x

BREQ-3, Behavioural Regulation in Exercise Questionnaire; EORTC-QLQ-30, European Organisation of Research and Treatment of Cancer Core Quality of Life Questionnaire; HADS, Hospital Anxiety and Depression Scale; MFSI-SF, Multi-dimensional Fatigue Symptom Inventory; MRS, Menopausal Rating Scale; MSFI-SF, Multidimensional Fatigue Syndrome Inventory- Short Form; PA, physical activity; PACES, Physical Activity Enjoyment Scale.

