#### PA and health measures

An accelerometer (GENEActiv, Activinsights) and sleep log will be administered at all evaluation time points to measure PA. Participants will be asked to wear the accelerometer on their non-dominant wrist 24/7 for 8 days at each time point. Valid data will be at least 3 days >16 hours of accelerometer data collected.^39^ Device-assessed PA will be the primary research outcome measure of interest in the subsequent pilot study and definitive main trial.

Participants’ belief in their ability to successfully complete incremental 5–50 min periods of walking at a moderate/brisk pace will be assessed via the self-efficacy for walking scale.^40^ Motivation for PA will be assessed using the Behavioural Regulation in Exercise Questionnaire.^41^ This is a 23-item scale which assesses motivation on a self-determination continuum. Enjoyment of PA will also be assessed via the original 18-item PACES scale.^42^

In relation to well-being, menopausal symptoms, such as hot flushes and sweating will be investigated using the Menopausal Rating Scale.^43^ Quality of life will be assessed using the EORTC QLQ-30, which is commonly used in gynaecological cancer populations and includes five functional scales, three symptom scales, a global health scale and a quality of life scale. The Hospital Anxiety and Depression scale (HADS),^44^ will be administered to measure symptoms of anxiety and depression. Fatigue will be assessed using the Multi-dimensional Fatigue Symptom Inventory (MFSI-SF),^45^ a measure which has been previously used to assess fatigue in a gynaecological cancer population.^23^

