#### Evaluation-related feasibility measures

Participant recruitment rates will be monitored by recording the number of identified potential participants, the number of those who express an interest in taking part, the number of those who are eligible and not eligible along with the reasons for ineligibility and the number who consent to participate. Retention and attrition rates will be monitored by recording the number of participants who withdraw from the study and the number who do not attend follow-up. Where possible, reasons for withdrawal will also be reported. The number of participants who complete the PA and health measures at each time point will be summarised.

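### One combined 20% rule covers questionnaires and accelerometer together, so the next trials' primary outcome has no completeness verdict of its own

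*Protocol article*

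**What the plan says.** Under the heading on the feasibility of the evaluation measures, the article gives one rule with one outcome. The measures pass as a whole when "no more than 20% of participants fail to provide questionnaire and accelerometer data at both baseline and week-24 follow-up". Table 3 places eight instruments under it, one accelerometer and seven questionnaires, all due at baseline and week 24.

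The section on PA and health measures gives the accelerometer a special role: "Device-assessed PA will be the primary research outcome measure of interest in the subsequent pilot study and definitive main trial". It also defines valid wear: "Valid data will be at least 3 days >16 hours of accelerometer data collected". The 20% rule does not refer to that definition.

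Two other statements bear on the point. The objectives include this one: "To determine compliance and completeness of evaluation measures at all time points". The section on evaluation-related feasibility measures adds: "The number of participants who complete the PA and health measures at each time point will be summarised". Neither sets a limit.

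The section on intervention components, directly before the 20% rule, handles its own threshold differently: "The threshold of feasibility for these rates will be 70% of participants complying, respectively". That rule includes wearing the PA monitor, which is the consumer device supplied as part of the intervention, not the research accelerometer.

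**The concern.** A feasibility criterion fixed in advance should answer the question that the next study will ask. Here that question is whether accelerometer data can be collected well enough to serve as a primary outcome. The two data types ask different things of participants: the accelerometer is worn day and night for 8 days with a sleep log, and the rest are questionnaires. Their completion rates may well differ.

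A combined verdict can then differ from the verdict that the accelerometer would earn alone. In which direction depends on how the word joining the two data types is read, and the text does not settle this. If accelerometer completion is reported only as a count, any judgement of it has to be made after the data are seen, which is what a threshold fixed in advance is meant to avoid.

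**Working it through.** **Inputs from the article.** Sample size about 30; limit 20%. The limit is set by decision and no calculation lies behind it, so there is nothing to reproduce beyond 0.20 × 30 = 6. The rule passes with at most 6 failures.

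**Assumptions.** The article gives no expected completion rates. Let q be the share providing questionnaire data and a the share providing accelerometer data, each at both required visits.

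**Formulas for the share failing.**
- Both types missing: (1 − a)(1 − q) if the two are independent; 1 − max(a, q) if the smaller missing group lies wholly inside the larger (nested).
- Either type missing: 1 − a·q if independent; 1 − min(a, q) if nested.

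**At q = 0.95, a = 0.75.**
- Both missing: 0.25 × 0.05 = 1.25% (independent) to 1 − 0.95 = 5% (nested). Below 20%, so success.
- Either missing: 1 − 0.75 = 25% (nested) to 1 − 0.7125 = 28.75% (independent). Above 20%, so the expected verdict is failure, although questionnaires are 95% complete.

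**Chance of passing with 30 participants.** P(pass) is the binomial probability of 6 or fewer failures, the sum over x = 0 to 6 of C(30, x) p^x (1 − p)^(30 − x), with p the share failing. The last column applies the same 20% limit to the accelerometer alone, so p = 1 − a.

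| a | q | Both missing: share failing, P(pass) | Either missing: share failing, P(pass) | Accelerometer alone: P(pass) |
|---|---|---|---|---|
| 0.85 | 0.95 | 0.75–5%, at least 0.999 | 15–19.25%, 0.85–0.65 | 0.85 |
| 0.75 | 0.95 | 1.25–5%, at least 0.999 | 25–28.75%, 0.35–0.20 | 0.35 |
| 0.60 | 0.95 | 2–5%, at least 0.999 | 40–43%, 0.02–0.01 | 0.02 |
| 0.95 | 0.70 | 1.5–5%, at least 0.999 | 30–33.5%, 0.16–0.08 | 0.999 |

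**What the rows show.**
- On the both-missing reading, a pass says almost nothing about the accelerometer. At 60% provision the combined rule still passes almost surely, while an accelerometer-only rule would pass with probability 0.02.
- On the either-missing reading, a pass means at most 6 of 30 lack anything, so at least 24 of 30 (80%) provided accelerometer data. A fail is uninformative: in the last row the rule passes with probability only 0.08 to 0.16, although the accelerometer alone would pass almost surely.
- In the first row the expected share failing is under 20% on every reading. The verdicts diverge in expectation only when one data type falls short of 80% or when modest losses in both add up.

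**The case against.** The strongest reply is that nothing is lost. Completion of the measures is to be counted at each time point, completeness of measures is a stated objective, and interviews on the evaluation measures are offered to everyone, including those who withdraw. A 75% accelerometer return beside a 95% questionnaire return would be visible there. This stands: the gap is a limit, not information.

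The either-missing reading is also the more natural one, and on it a pass protects the accelerometer. A reader might infer that the rule as written lets good questionnaire return hide accelerometer failure. The article supports this only on the both-missing reading. A third reading, with 20% applied to each data type, is grammatically possible and would remove most of the problem. However, the sentence gives a single verdict and lacks the component-by-component wording of the rule before it.

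A reader might further infer that the combined verdict would send the next trial in the wrong direction. Nothing in the article supports that. Results inform refinement and a larger trial if appropriate, and no decision hangs on this verdict alone.

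Nor does the point call for a verdict on each of the eight instruments. At a true 90% provision each would pass with probability 0.974, so all eight together, if independent, with only 0.974^8 ≈ 0.81. Nothing in the article suggests that the seven questionnaires will be returned at different rates.

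Finally, a journal article condenses a fuller protocol, which may contain instrument-level tables. That excuses absent detail, but the criterion itself is stated here, and its form is what needs changing.

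**Conclusion.** The point holds in a limited form. The article fixes one combined 20% criterion and sets no separate limit for accelerometer data, although those data are the intended primary outcome of the later trials. On the both-missing reading the rule can declare success with accelerometer data largely absent. On the either-missing reading a pass is informative about the accelerometer and only a fail is ambiguous, with the planned counts available to describe the cause.

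The size of the effect rests on assumed completion rates. The 95% and 75% pair is illustrative, and at 95% and 85% the expected share failing stays within the limit on every reading. This is a worthwhile and nearly free improvement to a rule stated in advance, not a flaw that threatens the study.

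**What to change.** Replace the combined criterion with two, each with the 20% limit:

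1. Accelerometer: no more than 20% of participants without valid data, using the article's own wear definition, at baseline and at week 24.
2. Questionnaires as a set: no more than 20% of participants without questionnaire data at the same two visits.

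Report two verdicts, and keep completion of each individual questionnaire descriptive, as already planned.

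The cost is a sentence and one extra line in a results table; no new data are needed. The downside is that one data type may be reported as failing, and with 30 participants each verdict is imprecise. An accelerometer with true provision of 75% would still meet the limit with probability 0.35, and one at exactly 80% would miss it with probability 1 − 0.61 = 0.39. Each verdict should therefore be read beside the observed count.

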#### PA data and questionnaire outcomes

Data from the accelerometer will be cleaned and processed in GGIR using *R programming* and analysed using *IBM SPSS statistics V.25*. Means and standard deviations (SDs) will be used to describe the PA from the accelerometer at each evaluation time point. Constructs measured via questionnaire will be analysed by standard scoring procedures. Questionnaire outcomes of interest will be reported on means (or medians where necessary) and SDs.

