## Methods and analysis

### Study design

This is a single-arm pre study and post study to assess the feasibility and acceptability of conducting and evaluating a PA intervention following treatment for cervical cancer. A process evaluation will also be conducted throughout the study.

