### Sample size

This study will aim to recruit approximately 30 participants. This sample size was chosen as it is a realistic target when considering cervical cancer incidence both in the UK and at UHL where recruitment will take place over the given time period. In line with recommendations from the National Institute for Health Research, a sample size of 30 is appropriate to answer the questions posed by a feasibility trial.^32^ The feasibility of lifestyle and PA interventions in endometrial and breast cancer survivors have successfully employed similar sample sizes.^27 33^

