#### The feasibility of study recruitment and retention

A priori, we have defined a recruitment success rate as recruitment of 30 participants in the first 3 months or that 75% of those identified as eligible are recruited, and a successful retention rate at week-24 as 70%.

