The current PA guidelines offered by the Government Chief Medical Officers do not specify recommendations for cervical cancer survivors.^30^ However, using a development framework that prioritises insights and experiences from the target population is a great strength of this intervention, as it allowed direct and effective tailoring of the intervention components despite specific recommendations not being available. Hence, the aerobic PA recommendations were deemed an appropriate target for women treated for cervical cancer.^29^ Additionally, the criterion to include women who are at least 6 months post treatment was also a decision informed by the need’s assessment, with the time between 3 and 9 months post treatment being identified as critical for intervention and for positive change.^49^ A limitation is that the protocol does not incorporate strength training, and therefore does not reflect the current PA guidelines for after cancer. However, as PA levels are generally low following cervical cancer treatment, it seemed appropriate to promote one PA modality which was realistically achievable (i.e., walking) to enhance adherence to the intervention.

This study will add to the current debate regarding the role of technology in promoting PA after cancer. The intervention uses a PA monitor and its associated online community and a messaging platform. Previous research supports the use of such e-health technologies in combination with health coaching over a shorter duration (4-week programme).^50^ However, it has been suggested that further investigation is needed to test the acceptability of such technologies in more diverse populations,^51^ to explore optimal intervention length and to question the maintenance of PA behaviour change.^50^ Although a limitation of this protocol is that statistically relevant changes in PA between time points will not be reported, trends in PA levels will provide data inferring the feasibility of promoting and maintaining PA behaviours. The process evaluation will also provide valuable insight regarding the acceptability of the components.

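### Activity trends read from separate visit means, in a single-arm study that tolerates dropout, cannot support the Discussion's inference about promoting and maintaining activity

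*Protocol article*

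**What the plan says.** The points below are all in the protocol article.

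- **Summary of accelerometer data** (PA data and questionnaire outcomes): "Means and standard deviations (SDs) will be used to describe the PA from the accelerometer at each evaluation time point". The article states no change within participants and no common set of women across visits.
- **Questionnaires** (same section): outcomes are to be "reported on means (or medians where necessary) and SDs".
- **Use of the summaries** (Discussion): after conceding as a limitation that statistical changes between time points will not be reported, the article says that "trends in PA levels will provide data inferring the feasibility of promoting and maintaining PA behaviours".
- **Design** (Study design): "This is a single-arm pre study and post study", so there is no comparator.
- **Size** (Sample size): "This study will aim to recruit approximately 30 participants".
- **Tolerated loss** (The feasibility of study recruitment and retention): "a successful retention rate at week-24 as 70" per cent. The feasibility of the evaluation measures sets a further limit for outcome data: "no more than 20% of participants fail to provide questionnaire and accelerometer data at both baseline and week-24 follow-up".
- **Entry** (Participants and recruitment): women must fall below the national activity guideline, judged by self-report over the previous 7 days.
- **Later use** (PA and health measures): device-assessed activity is named as the primary outcome of the subsequent pilot and main trial.

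**The concern.** A trend across visit means is a statement about change only if the same women contribute at each visit, or if those who leave resemble those who stay. The article secures neither, and it counts a 30% loss by week 24 as success. Week 24 is also the visit on which any statement about maintenance must rest. If less active women leave more often, the mean rises although no woman has changed. Readers of the results could not see this from a row of means and SDs.

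The single arm adds explanations that no summary of these data can exclude. Women are selected on a low recent week, so later values may drift up by regression to the mean. Baseline and week 24 also fall at different times of year.

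There are two lesser costs. Visit-wise SDs do not show the SD of change or the baseline-to-follow-up correlation, which would help in planning a later trial with this primary outcome. And a median chosen because data are skewed is not well described by an SD. The median option is given only for questionnaires, although accelerometer activity may be skewed too.

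**Working it through.** The article gives no effect size, SD or power figure for activity, so there is no planned figure to reproduce. What can be checked is how far a visit mean can move with no change in anyone.

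**Inputs from the article.** Target 30; retention 70% at week 24; at most 20% without outcome data.
- 30 × 0.70 = 21 women, 9 lost.
- 30 × 0.80 = 24 women, 6 without data. This reads the 20% limit against all 30 recruited.

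**Assumption.** Those lost were, at baseline, d SD less active than those who stayed, with d from 0.5 to 1.0. The article gives no value for d, nor its direction.

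**Formula.** Let f be the share retained. The baseline mean of everyone is f × (mean of stayers) + (1 − f) × (mean of leavers). If no woman changes, the later mean equals the stayers' baseline mean, so

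shift = (1 − f) × d.

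| | d = 0 | d = 0.5 | d = 1.0 |
|---|---|---|---|
| 70% retained (21) | 0 | 0.30 × 0.5 = 0.15 SD | 0.30 × 1.0 = 0.30 SD |
| 80% with data (24) | 0 | 0.20 × 0.5 = 0.10 SD | 0.20 × 1.0 = 0.20 SD |

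**Cross-check by another route.** Suppose activity level and the tendency to stay have correlation ρ (assumed). The expected shift is about ρ × φ(z)/f, where z is the (1 − f) normal quantile. Simulation of 20,000 studies of 30 women, with no change in anyone, gave:

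| ρ | 21 retained | 24 retained |
|---|---|---|
| 0 | 0 | 0 |
| 0.2 | 0.10 SD | 0.07 SD |
| 0.3 | 0.15 SD | 0.10 SD |
| 0.5 | 0.24 SD | 0.17 SD |
| 1.0 (least active all lost) | 0.48 SD | 0.34 SD |

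The two routes agree in scale. The last row is the ceiling.

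**What visit-wise SDs leave out.** With equal SDs at both visits and within-woman correlation r (assumed), SD of change = SD × √(2(1 − r)):
- r = 0.5: √1.0 = 1.00 SD
- r = 0.7: √0.6 = 0.77 SD
- r = 0.8: √0.4 = 0.63 SD

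The same pair of visit SDs fits all three.

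**What paired change would give.** With 21 pairs, the 95% half-width is t(0.975, 20) × SD of change / √21. This is about 0.46, 0.35 and 0.29 SD for r = 0.5, 0.7 and 0.8. Treating the 30 and the 21 as independent samples, because r is not reported, gives 1.96 × √(1/30 + 1/21) = 0.56 SD.

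**The case against.** The strongest reply is that this is a feasibility study. Its objective for these data is only to describe them, and visit-wise means and SDs do that. The lack of power is disclosed, a single arm is ordinary at this stage, and none of the feasibility criteria depends on activity levels or trends. Withdrawals, with reasons where possible, and the number completing the measures at each visit will be recorded, so n per visit will be visible. Paired change, correlations and analysis sets are often left to a fuller plan.

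Most of this stands. Describing the data is not the fault, and the absence of paired change alone would not be a finding. What does not fall away is the sentence in the Discussion. It attaches an inference to the visit summaries, and a fuller plan elsewhere would not remove it. Disclosing low power does not meet the point either: a larger sample would leave dropout, regression to the mean and season where they are.

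Three stronger readings are tempting, and the documents do not support them.

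- **That the article claims efficacy.** It speaks of the feasibility of promoting and maintaining activity, which is softer, and it concedes in the same sentence that statistical changes are not reported.
- **That season will account for most of any trend.** A 168-day gap is close to half a year, but the article gives no start date and no seasonal amplitude. The effect could be near nil or substantial, in either direction. Recruitment within 3 months is also only one of two alternative success criteria.
- **That the study can yield no SD of change.** The same women are measured repeatedly, so the data contain it. Only the planned summary leaves it out.

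**Conclusion.** The concern holds as a mismatch between a stated summary and a stated inference. At the retention the article calls successful, dropout alone could raise the week-24 mean by 0.15 to 0.30 SD, or by 0.10 to 0.20 SD if 80% provide data. Both ranges assume leavers 0.5 to 1.0 SD less active at baseline. If leavers do not differ, the expected shift is zero; if they are more active, it reverses. The 70% is a tolerated floor, not a forecast, so these figures show what could happen and do not predict a bias.

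Regression to the mean and season cannot be sized from the article. Regression may be partly spent by baseline, because women are screened by questionnaire and then measured by accelerometer; how much remains is unknown. Neither can be separated from an intervention effect without a comparator.

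The pairing of median with SD is a small error in the text as printed. No stated success decision turns on the trends. The point is therefore a correction worth making, and it does not threaten the study's main feasibility conclusions.

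**What to change.** 1. Keep the visit-wise summaries and print n beside each.
2. Add within-participant change from baseline (mean, SD, 95% CI) at weeks 6, 12 and 24, among women with valid accelerometer data at both visits.
3. Report the baseline-to-follow-up correlation, for use in planning the later trial.
4. Compare baseline activity of completers and non-completers.
5. Give median with IQR, not median with SD, for skewed variables, and extend this option to accelerometer activity.
6. Replace the Discussion sentence with wording such as: *Changes in device-assessed PA are descriptive and uncontrolled. They may reflect dropout, regression to the mean or season, and will not be used to infer that PA was promoted or maintained.*

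Item 2 removes the shift caused by dropout linked to a woman's stable activity level. It does not remove dropout linked to change itself, regression to the mean or season, which is why item 6 is needed as well.

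The cost is a few more lines of analysis on data already being collected, and a weaker statement about activity trends. The intervals will be wide, as the half-widths above show, and should be presented as such.
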